### Outcomes

Our primary outcome is satisfaction with care and is measured on a 0–10 numeric rating scale (NRS) at 12 months post-inclusion. Our secondary outcome is safety, which is evaluated and measured by recurrence, re-referral rate, complications following recurrence treatment and survival. For the secondary outcomes, patients will be followed for at least 1 year after inclusion. Safety outcomes are only assessed after the study termination, thereby aiming for at least 2 years follow-up per patient. All outcome measures are outlined in Table 1.

**Table 1 T0001:** Outcome measures.

Outcome measure	Assessment	Evaluation method	Timing of evaluation

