**Patient satisfaction (PREMs)**			
Overall satisfaction with care	0–10 NRS	Survey	Baseline, at 6 and 12 months
**Satisfaction with travel time**	0–10 NRS	Survey	Baseline, at 6 and 12 months
**Specific satisfaction**	Questions about satisfaction with care from CQI questionnaires [33, 35]	Survey	Baseline, at 6 and 12 months

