### Sample size and recruitment

A power analysis was performed to calculate the sample size needed to answer our primary research question. As telemedicine follow-up has not been studied in HNC patients, power analysis was based on data from non-oncologic populations [26–28]. Most of these studies are one-armed studies. These studies reported a mean patient satisfaction, measured with a NRS or VAS, of 8.6 to 8.8, with one study noting a baseline score of 8.2. Although these results may not be representative of the HNC population, we based our expectations with regard to the primary outcome on these studies, nonetheless. Patient satisfaction is estimated at 9 (standard deviation [SD] 1.8) in the intervention arm and 8 (SD 1.8) in the control arm. To detect a clinically relevant difference of 1 point with 80% power and a two-sided alpha of 0.05, at least 41 patients per group are required. With an expected drop-out of 10%, a total of 90 patients will be included. This analysis was performed using G*Power (version 3, Heinrich-Heine-Universität Düsseldorf, Germany). Patients are first informed about the study by their treating head and neck oncologist in the HNOC. If a patient meets the eligibility criteria, the researcher will provide additional information, and an informed consent will be obtained.

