### Data collection methods

Baseline characteristics collected from electronic patient files include age, gender, clinical and histological tumour data, (surgical) history and comorbidities. Comorbidities are graded using the Adult Comorbidity Evaluation (ACE-27) as none, mild, moderate or severe [29]. Follow-up data will be collected via patient files or surveys and stored in REDCap (Table 1). Only the researchers have access to this securely stored data.

Patients will complete a 39-question survey at baseline (Supplementary information C) and again at 6 and 12 months. The survey includes validated and new questions, developed with support from a clinical epidemiologist (KV) with expertise in questionnaires (Table 1) [30–35].

The baseline survey is completed on paper after inclusion but before randomisation. A shorter version is used during follow-up. Intervention group patients receive surveys at baseline or by mail and complete them during a scheduled call with researcher assistance if required. Patients followed at the HNOC complete surveys after follow-up visits, also with help if required.

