### Statistical analysis

Descriptive statistics will be used to summarise patient’s baseline characteristics. Categorical variables will be presented as absolute numbers and percentages of the total. Continuous variables are tested for normality using Kolmogorov-Smirnov analysis and will be presented as means and SDs for normally distributed data, and medians and interquartile ranges for non-normally distributed data. Between-group mean (or median) differences, rate differences and rate ratios with 95% confidence intervals (or ranges) will be calculated. The groups will be compared using the Wilcoxon signed rank test or the Mann-Whitney test for non-normally distributed data, the independent t-test for normally distributed data and chi-squared test for categorical variables. Additionally, within-group changes will be assessed with paired t-tests (continuous data) and the McNemar test (categorical data). Kaplan-Meier survival analysis will be performed for disease-specific and overall survival. The EQ-5D-5L, EORTC QLQ-H&N-35 and cancer worry scale (CWS) questionnaires will be analysed according to their manual [30–32, 34]. Total CO_2_ emission caused by travel to the hospital will be estimated and compared between groups based on the values provided by the European Environment Agency for the period 2010–2023 (130.1 g of CO_2_ per kilometre) [36]. Missing values will be handled using multiple imputation, assuming that there is only missingness at random, and all analyses will be performed on an intention-to-treat basis. The data will be reported according to the CONSORT guidelines [37].

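### The primary comparison is unadjusted although the same satisfaction score is collected before randomisation, which gives up precision at no saving

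*Protocol article*

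**What the plan says.** The Outcomes section of the protocol article fixes the endpoint: "Our primary outcome is satisfaction with care and is measured on a 0–10 numeric rating scale (NRS) at 12 months post-inclusion". Table 1 schedules the overall satisfaction item at "Baseline, at 6 and 12 months". The Data collection methods section places the first measurement ahead of allocation: "The baseline survey is completed on paper after inclusion but before randomisation".

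For comparing the arms, the Statistical analysis section names "the independent t-test for normally distributed data and chi-squared test for categorical variables", and the Mann-Whitney test where data are judged non-normal. It names no regression model, analysis of covariance, mixed model or baseline covariate. The only stated analytic use of repeated scores is a paired test of change within each arm. Multiple imputation is planned, without saying which variables feed it.

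The section Allocation to study groups rules out blocking and stratification, on the ground that no baseline characteristic is expected to affect the outcomes materially.

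**The concern.** A pre-randomisation score on the outcome's own scale cannot be affected by allocation and is the most obvious candidate predictor of the 12-month score. Leaving it out of the between-arm comparison keeps in the error term whatever variance it would explain, so the confidence interval is wider than it need be.

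The design offers no substitute. With simple, unstratified allocation, a chance difference in baseline satisfaction is dealt with neither when patients are allocated nor when they are analysed. The within-group tests do not help, because a change within one arm, or two such changes viewed side by side, is not a test of the difference between arms.

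At stake are the width of the primary interval and the trial's power. The validity of the test is not at stake.

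**Working it through.** **Inputs (Sample size and recruitment).** The section assumes means of 9 (intervention) and 8 (control) with a common SD of 1.8. Its target is stated as "To detect a clinically relevant difference of 1 point with 80% power and a two-sided alpha of 0.05". The resulting requirement is given as 41 per group before drop-out. So δ = 1, σ = 1.8, δ/σ = 0.556 and n = 41 per group.

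**Step 1: the plan's own figure.** With these inputs, a two-sided t-test at 0.05 needs 51.8, so 52 per group (51 by the normal approximation). The stated 41 is reproduced only with a one-sided alpha of 0.05 (40.8, rounded up). That is a separate sample-size error. Here it only sets the starting point.

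**Step 2: unadjusted power at 41 per group.** The noncentrality is (δ/σ)·√(n/2) = 0.556 × √20.5 = 2.515 on 2n − 2 = 80 degrees of freedom, which gives 70.0%. With all 90 patients retained (45 per group) it is 74.1%.

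**Step 3: power with baseline as covariate.** Let rho be the correlation between baseline and 12-month scores within arms. The residual SD is 1.8·√(1 − rho²), the noncentrality becomes 2.515/√(1 − rho²), and the degrees of freedom are 2n − 3 = 79. The approximate 95% half-width is 1.99 × residual SD × √(2/41). The documents give no rho, so a range is shown.

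| rho (assumed) | Variance removed | Residual SD | Half-width of 95% CI | Power at 41 per group | n per group for 80% |
|---|---|---|---|---|---|
| 0 | 0% | 1.800 | 0.79 | 70.0% | 52 |
| 0.2 | 4% | 1.764 | 0.78 | 71.8% | 50 |
| 0.3 | 9% | 1.717 | 0.75 | 74.0% | 48 |
| 0.4 | 16% | 1.650 | 0.73 | 77.4% | 44 |
| 0.5 | 25% | 1.559 | 0.69 | 81.8% | 40 |
| 0.6 | 36% | 1.440 | 0.63 | 87.4% | 34 |

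At 41 per group, 80% power is reached at rho of about 0.46; at 45 per group, at about 0.37. If rho is really zero, the lost degree of freedom costs about 0.01 percentage points of power.

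**Step 4: size of a chance imbalance.** Assume the baseline SD is also 1.8. The standard error of the baseline difference is then 1.8 × √(2/41) = 0.40. A gap of at least 0.5 points (0.5/0.40 ≈ 1.26 standard errors) arises in about 21% of randomisations. At rho 0.5 with equal SDs the regression slope is 0.5, so such a gap would be expected to move the unadjusted 12-month difference by 0.5 × 0.5 = 0.25 points, against a target of 1.

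**The case against.** **Unadjusted does not mean biased.** A reader might infer that leaving out baseline biases the primary estimate or makes the test invalid. The documents do not support that. A comparison of randomised arms is unbiased over randomisations, and its confidence interval already allows for chance imbalance. What is lost is precision, and accuracy given the imbalance that actually occurs.

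**The correlation may be low.** This stands. Controls continue at the oncology centre, but the 12-month score in the intervention arm rates different care: a local surgeon with remote review. Eligibility requires only that patients be within two years of surgery, so some may enter with little experience of follow-up. Expected means of 8 and 9 on a scale capped at 10 may also weaken the correlation. As an illustration with assumed values, rho of 0.5 in controls and 0.2 in the intervention arm pool to about 0.35, for power of about 75.6%. The gain may be modest, but the cost is close to nil even at rho zero.

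**The t-test may not be the test used.** This also stands. A mean of 9 with SD 1.8 under a ceiling of 10 is likely to be skewed, so the normality check may lead to Mann-Whitney. The 70.0% applies to the t-test only, and a linear model would replace both branches. The fix has to say so.

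**Covariates can be left to an analysis plan.** This carries less weight here. The article does not stay silent: it states which tests will compare the arms, and those tests are unadjusted. Imputation that drew on baseline scores would still leave the comparison itself unadjusted.

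**Conclusion.** The point holds as a matter of efficiency. The protocol names unadjusted tests for its primary comparison while already collecting a pre-randomisation score on the same scale. With the plan's own δ, SD and 41 per group, adjustment raises two-sided power from 70.0% to between 71.8% and 87.4% as rho runs from 0.2 to 0.6. These figures assume a linear relation, equal SDs in the two arms and approximate normality. Rho itself is an assumption throughout.

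A reader might also infer that adjustment would restore the planned 80% power. The documents do not support that, because they give no correlation, and below about 0.46 the target is still missed at 41 per group. The sample-size figure needs its own correction. If it is corrected, baseline adjustment remains a worthwhile gain in precision. It is an improvement that should be made, not a flaw that invalidates the trial.

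**What to change.** In the Statistical analysis section, prespecify the primary analysis as a linear model of the 12-month overall satisfaction score on randomised arm, with the baseline score as covariate, reporting the adjusted mean difference with its 95% confidence interval. State that this replaces the normality-dependent choice between t-test and Mann-Whitney. Because skew is likely, add a rank-based analysis or one with robust standard errors as sensitivity.

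A mixed model using all three time points is an acceptable alternative only if baseline enters as a covariate or the baseline means are constrained to be equal across arms. An ordinary arm-by-time model with free baseline means returns, with complete data, the raw 12-month difference and so adjusts for nothing.

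The same form can serve the other continuous scores measured at baseline: travel-time satisfaction, the EQ-5D-5L visual analogue scale, the H&N35 scales and the cancer worry scale. Label the within-group tests as descriptive.

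The cost is a few sentences, with no new data and no extra patients. The change should be fixed before outcomes are analysed, so that the choice to adjust cannot look data-driven.

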### Eligibility criteria

Inclusion criteria include patients who underwent TOLS for severe dysplasia, carcinoma-in-situ or T1 squamous cell carcinoma, have a one-way travel time (by car) to the HNOC of > 45 min and have the possibility of follow-up in a nearby participating hospital. In addition, patients are eligible for inclusion if they are within 2 years postoperatively and can speak and write Dutch (Figure 1). Patients will be excluded if they continue to undergo follow-up for other cancers in the HNOC. Written informed consent will be obtained from all patients (Supplementary information B).

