**Other**			
Visit frequency	Amount of visits (scheduled and extra visits)	Electronic patient file	End of follow up period
**Travel distance**	Total distance travelled (kilometres) from the patient’s home address to the hospital by car	As indicated by Google Maps	End of follow up period
**Travel time**	Subjectively reported travel time, for the patients and their care givers	Survey	Baseline and at 6 months
**CO_2_ emission**	Estimation of CO_2_ emission caused by travel to the hospital for follow-up	Calculated from the travel distance (kilometres) and the mean emission per kilometre [36]	End of follow up period

Abbreviations: PREMs: patient-reported experience measures; NRS: numeric rating scale; CQI: consumer quality index; PROMs: patient-reported outcome-measures; HRQoL: health-related quality-of-life; VAS: visual analogue scale; CWS: cancer worry scale; EORTC QLQ-H&N-35: European Organisation for Research and Treatment of Cancer Quality of Life Questionnaire Head and Neck Module 35; CO_2_: carbon-dioxide.

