### Allocation to study groups

An independent researcher will generate the randomisation chart to ensure allocation concealment for the patient, clinician and researcher. Randomisation will be performed in REDCap with a 1:1 allocation ratio. Block randomisation and stratification will not be used, as no baseline characteristics are expected to significantly influence the study outcomes. Blinding of the treatment allocation after randomisation is not feasible, as both patients and care providers will be aware of the hospital setting in which the follow-up takes place.

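### Travel distance and CO2 are compared without adjustment, although two distances known before randomisation for every patient largely determine them; adjusting would narrow the interval at almost no cost

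*Protocol article*

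**What the plan says.** Table 1 (section Other) defines travel distance as "Total distance travelled (kilometres) from the patient’s home address to the hospital by car", with the source given as "As indicated by Google Maps". CO2 is this distance times a mean emission per kilometre, set at 130.1 g in the Statistical analysis section. That section says that total CO2 "emission caused by travel to the hospital will be estimated and compared between groups". For continuous outcomes its between-group methods are rank tests and "the independent t-test for normally distributed data and chi-squared test for categorical variables". No covariate is named.

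The Eligibility criteria require that patients "have a one-way travel time (by car) to the HNOC of > 45 min and have the possibility of follow-up in a nearby participating hospital". This applies to both arms.

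The section Allocation to study groups states that "Block randomisation and stratification will not be used". The reason given is that no baseline characteristic is expected to have a significant influence on the outcomes. The Interventions section expects at least 4 to 6 consultations and regards a hospital as closer if it cuts travel time by more than one-third.

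**The concern.** Each patient's total is home-to-hospital distance times number of visits, and CO2 rescales that total by a constant. An unadjusted comparison uses only the distance of the allocated route. The difference between arms then carries the effect of relocating follow-up plus the chance difference in where the patients of the two arms live. That second part is noise that can be measured. Home address fixes both distances before allocation, and the mapping tool already in use gives both for every patient.

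The reason given for not stratifying does not hold for these two outcomes, because home location is a direct factor of both. What is at stake is the width of the interval around the reported saving, and protection against a chance imbalance in home distance.

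**Working it through.** **Plan's own figure.** The article gives no expected distance, saving or precision for these outcomes, so there is nothing to reproduce. The distances below are assumptions.

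**Inputs.** From the article: 90 patients, 1:1 (taken as 45 per arm), and 130.1 g per km. Assumed: visits V of 4, 5 or 6 with equal probability, independent of distance; round trips; one-way HNOC distance H and nearby distance L uniform and independent over three ranges. Then mean(V) = 5, var(V) = 2/3 and E[V²] = 25.67.

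**Formulas for the difference in mean kilometres per patient.**
- Saving = 2 × 5 × (mean H − mean L).
- Unadjusted variance = (4/45) × [var(VH) + var(VL)], where var(VH) = E[V²]·E[H²] − (5 × mean H)², and likewise for L.
- Adjusted variance (both distances, interactions with arm) = visit part + home part. The visit part is (4/45) × (2/3) × (E[H²] + E[L²]). The home part is 100 × (var H + var L)/90.

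**First scenario in full (H 60–140 km, L 5–45 km).**
- Saving = 10 × (100 − 25) = 750 km.
- var H = 80²/12 = 533.3 and E[H²] = 10,533.3. var L = 40²/12 = 133.3 and E[L²] = 758.3.
- Unadjusted: (4/45) × (20,355.6 + 3,838.9) = 2,150.6, so the half-width is 1.96 × √2,150.6 = 90.9 km.
- Adjusted: 669.1 + 740.7 = 1,409.9, so the half-width is 1.96 × √1,409.9 = 73.6 km.

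**All three scenarios (95% half-widths).**

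| H, L (km) | Saving (km) | Unadjusted | Adjusted | Narrower by |
|---|---|---|---|---|
| 60–140, 5–45 | 750 | 90.9 | 73.6 | 19% |
| 60–100, 10–40 | 550 | 58.5 | 50.4 | 14% |
| 70–160, 5–30 | 975 | 97.2 | 79.7 | 18% |

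Simulated trials agree: 91, 58 and 98 km unadjusted against 74, 50 and 80 km with regression on both distances. In CO2, the first row is 750 × 0.1301 = 97.6 kg, with half-widths of 11.8 and 9.6 kg.

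**Sensitivity.**
- If patients who live further away attend less often, the regression still estimates the true saving and its interval is 9–12% narrower.
- If the nearby distance is tied to the HNOC distance, the gain can be larger. With HNOC mean 85 km (SD 20), nearby distance 40–66% of it and 4–6 visits, the standard error falls from 5.6 to 3.6 kg on a saving of 52 kg.
- The size of the gain therefore depends on geography that the article does not give. Every scenario tried showed a gain with regression.

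**The case against.** The strongest reply is that nothing stated is wrong. Comparing observed totals between randomised arms is an unbiased intention-to-treat estimate, and its interval already allows for chance imbalance in home distance. A reader might infer that the comparison is biased, or that the saving itself is in doubt. The documents support neither. In the first scenario the unadjusted saving is 750/√2,150.6, about 16 standard errors from zero. Adjustment moves the half-width only from 12.1% to 9.8% of the saving. The flat emission factor also adds uncertainty that neither interval shows. All of this stands, and it is why the point is minor.

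A second reply is that a condensed article may leave covariates to a fuller document. That stands in part. However, the article does name its between-group tests, and they are unadjusted, so this is a stated choice.

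Three stronger readings should be resisted:
- Using both routes for all 90 patients would halve the variance of a per-visit saving if the two distances are uncorrelated, which makes the interval 29% narrower. But the outcome is total distance over follow-up, and variation in visits remains.
- Mean visits times mean distance, taken over all patients, may look like an equivalent shortcut. It is not equivalent if visit number depends on distance. In runs where distant patients attended less, it overstated the saving (749 against 723 km in the first scenario, about 4%) and lost its precision gain.
- A total compared between groups could be read as a sum over each arm. The text does not say so, and a per-patient total is the likelier meaning.

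**Conclusion.** The point holds as a loss of precision, not as an error. Kilometres and CO2 are compared by unadjusted tests although two pre-randomisation distances largely determine them. Adjusting for both would narrow the 95% interval by roughly 10 to 20%, under assumed distances and 4 to 6 visits. The direction of the conclusion would not change in any scenario tried. The exact gain rests on assumptions about where patients live and how visits relate to distance. Priority: optional, low-cost improvement to a secondary outcome. The article presents sustainability as an aim, so the CO2 figure is likely to be quoted, and a tighter estimate is worth one sentence in the plan.

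**What to change.** 1. Record the mapped distance from home to the HNOC and from home to the nearby participating hospital for all randomised patients, in both arms.
2. Keep each patient's observed total kilometres as the outcome: all actual visits, with re-referral trips counted at the HNOC distance. Multiply by 130.1 g for CO2.
3. Compare the arms by linear regression on arm, adjusted for both distances (centred) with arm-by-distance interactions and robust standard errors. Report the saving with its 95% confidence interval.
4. State whose saving is estimated. Ordinary robust standard errors treat the centring means as fixed, so they describe the randomised patients and leave out the home part of the variance. In the first scenario that gives 1.96 × √669.1 = 50.7 km instead of 73.6 km. If the saving is meant for a wider population, bootstrap patients and re-centre in each sample.
5. Do not replace this with mean visits times mean distance.

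The cost is one extra map look-up per patient and a slightly more complex analysis. No change to recruitment, allocation or visits is needed.

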## Discussion and conclusion

This is the first prospective study investigating the novel concept of relocating follow-up care for HNC patients. Since the COVID-19 pandemic, telemedicine use has notably increased and is widely accepted by both oncologic and non-oncologic patients [26–28, 38]. In most telemedicine studies in otolaryngology, videoconferencing consultations are used, with remote physical examinations occasionally employed for otoscopic evaluations but not for laryngoscopic (follow-up) assessments [39, 40]. Advancements in HD-laryngoscopy and emerging Artificial Intelligence (AI) disease detection software may create opportunities to reorganise follow-up care for HNC patients, reducing dependency on physician expertise [41, 42].

The strength of the study is its RCT design and the inclusion of a preference arm. This study aligns with sustainability goals. The possibility of telemedicine follow-up offers a more flexible and patient-centred approach to care, reducing travel burden and increasing accessibility. It may also help alleviate pressure on specialised centres by enabling efficient, remote monitoring without compromising safety. A limitation of the study is the use of a non-validated survey. However, most questions are derived from validated questionnaires, and the benefit of validation of the survey was not seen. Additionally, patients in the intervention group will complete the survey in a different setting than those in the control group (i.e. at home with remote assistance through a telephone call and at the HNOC with assistance in person as needed), which may introduce bias. With the knowledge that a follow-up duration of 12 months is limited, safety outcomes will only be assessed after the conclusion of the study period. Furthermore, travel distances to hospitals in the Netherlands are typically shorter than in other countries; however, the findings of this study may also be applicable to larger countries, where they could potentially benefit an even greater number of patients. If patients are satisfied and safety is confirmed, future research should explore other patient groups suitable for telemedicine follow-up. Multicentre studies will be necessary to assess its national impact and inform guideline changes, benefiting patients, society and the environment.

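### Missing 12-month satisfaction is imputed under missing-at-random only, although the outcome may itself influence who leaves and the survey route depends on where the patient is followed

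*Protocol article*

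**What the plan says.** The protocol article, under Outcomes, defines the endpoint: "Our primary outcome is satisfaction with care and is measured on a 0–10 numeric rating scale (NRS) at 12 months post-inclusion". Under Allocation to study groups it accepts that patients know their arm: "Blinding of the treatment allocation after randomisation is not feasible".

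Under Statistical analysis it gives one rule for missing data, "Missing values will be handled using multiple imputation, assuming that there is only missingness at random", and adds that "all analyses will be performed on an intention-to-treat basis". Under Sample size and recruitment the allowance for loss is a single overall figure: "With an expected drop-out of 10%, a total of 90 patients will be included". It is not split by arm and no reasons for leaving are given.

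The survey routes are described under Data collection methods. For one group: "Intervention group patients receive surveys at baseline or by mail and complete them during a scheduled call with researcher assistance if required". For the other: "Patients followed at the HNOC complete surveys after follow-up visits, also with help if required". The Discussion concedes that "patients in the intervention group will complete the survey in a different setting than those in the control group" and that this may bias results. It treats the matter as an effect of setting on the answers, not as an effect on who answers.

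**The concern.** Missing-at-random means that, given the observed data, the chance of a missing score does not depend on the score itself. Here the score is satisfaction with a follow-up route that the patient knows and experiences. Each arm has its own plausible source of discontent: control patients keep a journey of more than 45 minutes, and intervention patients give up examination in person at the HNOC. A patient who leaves because of this would have a low score that is never seen.

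The collection procedure adds a second problem. The HNOC survey follows an attended visit, whereas the intervention survey is completed in a call. As described, a control patient who stops attending, or who moves follow-up away from the HNOC, has no stated occasion to answer. An intervention patient who misses a local visit can still be reached by the call.

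If leavers score lower than their imputed values, the mean of that arm is too high. If this happens more in one arm than in the other, the primary between-group difference is biased. An intention-to-treat comparison relies on outcomes from exactly these patients.

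**Working it through.** **Inputs from the article (Sample size and recruitment; Allocation):** expected means 9 and 8, SD 1.8 in each arm, target difference 1 point, 80% power, two-sided alpha 0.05, 41 per group required, 90 in total, 10% drop-out, 1:1 allocation.

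**Inputs assumed, because the documents give none:** the missing fraction in each arm, and the number of points d by which leavers truly score below their imputed value (range 1 to 3, with 4 as a stress value).

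**1. The plan's own figures.**
- Drop-out: 90 × 0.9 = 81, close to 2 × 41 = 82. So 10% loss is about 4 to 5 patients per arm of 45.
- The 41 per group does not reproduce with a two-sided test. 2 × (1.960 + 0.842)² × 1.8² / 1² = 50.9, so 51 per group, or 52 with the t distribution. With one-sided alpha 0.05 the answer is 41. At 41 per group the two-sided power is about 70%. This is a separate issue. It matters here only because the trial has little margin to absorb bias.

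**2. Standard error of the difference.**
- 45 per arm: 1.8 × √(2/45) = 0.38.
- 41 per arm: 1.8 × √(2/41) = 0.398.

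**3. Bias of the imputed difference (intervention minus control).** With missing fractions m_I and m_C and shifts d_I and d_C:

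bias = m_I × d_I − m_C × d_C

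| Scenario (assumed) | d = 1 | d = 2 | d = 3 |
|---|---|---|---|
| 10% missing in both arms, shift in intervention arm only | +0.1 | +0.2 | +0.3 |
| 10% missing in both arms, shift in control arm only | −0.1 | −0.2 | −0.3 |
| 10% missing in both arms, same shift in both | 0 | 0 | 0 |
| 5% intervention, 15% control, same shift | −0.1 | −0.2 | −0.3 |
| 20% missing, shift in intervention arm only | +0.2 | +0.4 | +0.6 |

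A plus sign means that the intervention advantage is overstated, and a minus sign that it is understated. The stress value at 10% is 0.10 × 4 = 0.4.

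**4. Tipping point.** Take an observed difference of exactly 1 point, 41 per arm, and hold the standard error fixed. The difference needed for significance is 1.96 × 0.398 = 0.78, which leaves 1 − 0.78 = 0.22 points of room. Intervention leavers would have to lie 0.22 / 0.10 = 2.2 points below their imputed values at 10% missing, or 0.22 / 0.20 = 1.1 points at 20% missing. A shift in the control arm cannot remove significance from such a result, because it moves the true difference upward.

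**The case against.** Five counter-arguments deserve weight.

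- **Missing-at-random is a usual main assumption, and the article is a condensed document.** This stands. The clause does not rule out a sensitivity analysis, and the imputation model and any such analysis may be in a full protocol or analysis plan that is not shown. Their absence from the article is not the point made here. The point is a stated assumption set against a stated collection procedure that differs between groups. An analysis plan cannot recover scores that were never collected.
- **Switching is not missingness.** This stands for one direction. The HNOC survey route is worded by place of follow-up, so an intervention patient who returns to the HNOC would still be surveyed, and would be analysed as randomised. It does not cover a control patient who leaves the HNOC.
- **The text describes the usual route and forbids no other contact.** This is fair. Satisfaction is scheduled at 6 and 12 months for everyone, and staff may in practice telephone a control patient who does not attend. Equally, nothing says that an intervention patient who withdraws still takes the call. Differential loss is therefore a possibility, not a certainty.
- **Earlier scores may absorb part of the dependence.** This stands. Baseline and 6-month satisfaction are collected, and an imputation model that uses them would reduce the shift.
- **The one asymmetry in the text is conservative for the hypothesis.** This is largely right. Losing dissatisfied control patients would understate the expected advantage of 9 against 8. An estimate that is too small is still biased, however, and the opposite loss is not excluded.

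A reader might go further and infer that dissatisfaction drives withdrawal, that leavers will probably be imputed too favourably, and that the arms will be affected unequally. The documents do not support this. They give no reasons for drop-out and no split by arm, and patients unwilling to be randomised can decline and join the preference group.

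**Conclusion.** The point holds in a limited form. The article rests the analysis of an unblinded satisfaction outcome on missing-at-random alone, while its survey procedure makes response depend on attendance in one place of follow-up and not in the other. Leavers may be imputed too favourably, possibly unequally by arm.

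At the planned 10% drop-out the likely size is modest: 0.1 to 0.3 points if leavers in one arm only score 1 to 3 points below their imputed values. That is 10% to 30% of the 1-point target and less than one standard error. It could decide a result close to the target if intervention leavers were about 2.2 points lower, which is about 1.2 SD (2.2 / 1.8). The shifts, the per-arm loss and the 20% scenario are all assumptions. The sign cannot be determined from the documents, and the bias is zero when loss and shift are equal in both arms. This is a worthwhile, cheap improvement, not a flaw that undermines the design.

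**What to change.** 1. Offer the 12-month satisfaction item by mail or phone to every randomised patient who has not withdrawn consent, in both arms, whether or not a visit took place and whether or not the patient changed route. This matters most, because it has to happen during the trial.
2. State that the baseline and 6-month satisfaction scores enter the imputation model.
3. Keep missing-at-random as the main analysis and drop the implication that it is the only assumption examined. Add a delta-adjusted (tipping-point) sensitivity analysis in which imputed scores are lowered by 0 to 4 points, separately in each arm. Report the shift at which the conclusion changes.

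If a full protocol or analysis plan already contains items 2 and 3, a reference to it is enough.

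The cost is a few more contacts (about 4 to 5 expected leavers per arm) and one extra analysis, with no additional patients. The reported result may look less certain.
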